### Sample processing

The sample collection, processing and storage procedures will be performed in a standardised manner based on protocols described in detail in the INTERBIO-21st Operations Manual that has been developed with the assistance of the GAPPS team, and researchers at the Universities of Oxford and Cambridge, and Johns Hopkins Bloomberg School of Public Health.

In brief, maternal and cord blood samples will be collected to store whole blood, plasma and the buffy coat for a wide range of purposes, including DNA extraction for genetic and epigenetic studies and micronutrient assays. Two placental biopsies will be taken for immunohistochemistry and DNA extraction and in RNA later for expression studies (if the sample is obtained  $<30$  mins after delivery). In addition, we intend to collect and store samples for a number of future, as yet unspecified, biomarker assays relating to preterm delivery and fetal growth.

It is vitally important to ensure that samples are collected in a standardised way with adequate monitoring of quality control, principally because sample quality, quantity and handling can greatly influence the results of microarray and sequencing experiments.

The primary reason (aside from quality control) for ensuring that samples are collected, stored and processed in a uniform manner is to facilitate the anticipated interchange of data, in the future, with other biobanks. Standardising phenotypic definitions, sample collection methods and analyses fosters trans-national collaboration and networking. We shall therefore also seek advice from groups such as the Public Population Project in Genomics (<http://www.p3g.org>), which promotes international harmonisation and collaboration in population genomics and biobanking by sharing research tools and expertise.

**Faecal samples:** We wish to collect a faecal sample from mothers, opportunistically at the time of delivery, for metabiomic studies. Although it has been suggested that we should also collect stool samples from infants every 6 months, we feel that this is a rather large-scale undertaking that is beyond our remit.

We certainly appreciate the importance of looking for maternal intestinal co-infections and microbiota. In fact, we published on this subject in 1989: in a prospective study of 14,914 pregnant Guatemalan women, the incidence of IUGR increased with the number of parasitic species detected.

### Sample size

This is a great challenge in any field-study of this magnitude and even more difficult when exploring risk factors with relatively unknown degrees of association and prevalence in the population. The key issue is to reach a balance between logistical demands, including the need to maintain data quality in these populations, and power calculations especially for the planned epigenetic studies. Having said that, our co-investigators, [name] and [name] in the Wellcome Trust Centre for Human Genetics, Oxford, have considerable experience of conducting candidate gene and genome-wide association studies (GWAS) in related fields and the lessons learned over the last 15 years will be pertinent to the proposed studies.

To illustrate the point, Cardon & Zondervan reviewed how the complex interplay between genotype, phenotype, environmental factors and sample size affects the ability to detect disease susceptibility variants in population-based association studies. They concluded that thousands of cases and controls are required to detect common variants with small effect sizes in such studies.

Three examples demonstrate the need to study large numbers to identify genes influencing quantitative traits involved in metabolic function, such as birth weight. Nearly 120,000 individuals were genotyped to identify three loci influencing anthropometric measures (waist circumference and waist-hip-ratio) of central obesity and fat distribution in a recently published meta-analysis of 16 GWAS, followed by large-scale replication testing. Using similar methodology (GWAS meta-analysis followed by replication), over 90,000 individuals were genotyped to confirm that two loci are associated with BMI and to identify six additional loci and, more recently, nearly 40,000 European individuals were genotyped in identifying variants in *ADCY5* and near *CCNI* associated with fetal growth and birth weight.

For the nested case-control studies, we are collecting samples from 2,000 controls; and 2,000 cases from pregnancies with adverse outcomes, e.g. delivery at <38+0 weeks' gestation, term IUGR/SGA. In addition, we have the potential to include 400 cases and 2100 controls from the FGLS population in the analysis, taking into consideration the possibility of selection bias in the selection of FGLS population controls.

It is very unlikely that fewer than these numbers will be needed to study the effects of adverse intra-uterine effects on epigenetic profiles, especially as there is emerging evidence from genome-wide epigenetic studies in animals that imprinted quantitative trait loci (iQTL) affect body weight and growth and adult body composition in much more complex and diverse patterns than previously assumed.

**Selection of study centres** We aim to use the same rigorous processes to select the new sites for this extension as originally adopted in the selection of the current INTERGROWTH-21st centres. However, in this case, the selection criteria will inevitably involve finding a balance between obvious opportunities (e.g. having access to a malnourished pregnant population with a high prevalence of malaria/HIV) and the risks of working in a research naïve environment with limited existing access to antenatal care.

The criteria the INTERBIO-21st Steering Committee will use to select the centres will include factors such as: 1) existing research infrastructure and capacity; 2) existing maternity services, including antenatal ultrasound; 3) support of local health authorities; 4) previous experience in collecting biological samples; 5) geographical location to retain global coverage; 6) prevalence of key exposure variables, i.e. risk factors; 7) costs; 8) leveraged funding from other donors, and 9) need ideally for all samples in the proof-of-concept study to be analysed in a centralised facility.

## Staged introduction of sample collection at likely study sites

### Phase I

Shoklo Malaria Research Unit, Mae Sot, Thailand

KEMRI-Coast Centre for Geographical Medicine & Research, Kilifi, Kenya

John Radcliffe Hospital, Oxford, UK

### Phase II

The Aga Khan University Hospital, Nairobi, Kenya

Aga Khan University Medical Centre, Karachi, Pakistan

University of Witwatersrand, Johannesburg, South Africa

Universidade Federal de Pelotas, Pelotas, Brazil

## PROGRAMME II: Proof-of-concept study

### Background

Understanding the gene-environmental interactions underlying the plasticity of the epigenome at certain times from fetal life to infancy will be crucial to developing interventions, particularly in pregnancy, that might correct or at least prevent the long-term, adverse consequences. We believe that the key to doing so effectively is to recognise that phenotypes other than birth weight and gestational age alone are needed to determine the nutritional status of the newborn and assess the effectiveness of interventions.

The redefinition of newborn phenotypes will arise from evaluating a combination of factors in pregnancies with normal and abnormal outcomes. These include maternal health; fetal growth patterns measured using 2D ultrasound; growth patterns of individual fetal organs measured using 3D ultrasound; newborn body composition and physiological function; micronutrient levels and data from epigenetic experiments, which will initially characterise normal variability across the epigenome in uncomplicated pregnancy and then, in carefully designed nested case-control studies, evaluate the effects of adverse environmental and nutritional factors on the epigenome (and other biomarkers) in a pool of complicated and uncomplicated pregnancies.

### General Objectives

The aim is to conduct a hypothesis-testing, proof-of-concept study comparing 500 normal birth weight and 500 term IUGR/SGA newborns (using both cord blood and placental samples) taken from the samples collected in the context of both the INTERBIO-21st Fetal and Newborn Studies. This will be the first in a series of experiments utilising samples collected for the INTERBIO-Bank.

We aim to assess DNA methylation patterns in ~100 imprinted genes previously implicated in fetal growth. Our hypothesis is that maternal micronutrient deficiency, particularly of folate and other methyl donor factors, results in impaired fetal growth, development and pregnancy outcomes, through altered DNA methylation.

We will therefore correlate these methylation patterns with pregnancy (clinical outcomes, fetal growth), nutritional (micronutrient assays), and neonatal (growth, development and body composition) data, which will allow us to:

1. Study the effects of environmental and nutritional factors on the epigenome;
2. Develop new phenotypic definitions of LBW and other adverse pregnancy outcomes

If validated, the results could inform knowledge-based actions to address underlying problems, such as poor nutrition and infection, leading to improved outcomes. The data will, in addition, serve to define normal variability in the epigenome and inform the design of future epigenome-wide studies, once the cost has fallen, as inevitably it will with technological advances.

In the long-term, we would also wish to correlate these epigenetic findings with single nucleotide polymorphism (SNP) genotyping data from a GWAS given the increasing evidence that epigenetic regulation is influenced by genetic factors and the recently published data implicating variants in *ADCY5* and near *CCNI* with fetal growth and birth weight.

### Specific Objectives

We plan to study the methylation profiles of the ~100 imprinted genes that have to date been implicated in fetal growth, although the final list of candidate genes will be taken from our own systematic search of the literature, as well as existing databases, such as <http://www.geneimprint.com> and <http://igc.otago.ac.nz>.

Where possible, we will analyse cord blood and placental tissue separately to compare the methylation profiles of both tissues. The underlying rationale is as follows:

- There is increasing evidence that placental function and gene expression respond to, and are marked by, environmental insults. The placenta can therefore serve as a 'record of *in utero* exposure and pathology'. Effects on the fetus almost certainly occur downstream of these events and so comparing the epigenetic profiles of both tissues in individual pregnancies may help to differentiate the various causes of IUGR/SGA and preterm delivery.
- Alterations in DNA methylation in humans appear to be tissue-specific:
  - Katari et al. (2009) have reported significantly different DNA methylation levels at specific CpG sites between cord blood and placenta.
  - Guo et al. (2008) have described similar findings in two imprinting clusters: the H19 promoter is unmethylated and IGF2 DMR2 hypomethylated in placenta. However, in cord blood, these two regions maintain the differential methylation status seen in most other tissues.
  - Yuen et al. (2009) have observed DNA methylation of the promoter in *TUSC3* and *WNT2* in placental, and not the associated fetal, tissues; within individual placentas, methylation was confined to trophoblastic chorionic villi, and not amnion, chorion, cord or decidua.

### Study design

For this proof-of-concept study, we will randomly select 500 term IUGR/SGA cases from the INTERBIO-Bank. The 500 normal birth weight controls will be taken either from the population at least risk within the INTERBIO-21st Fetal Study or from the total with normal outcomes from the entire study population, and matched with the cases. A final decision will be made by the INTERBIO-21st Steering Committee.

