- PROGRAMME I: Create a unique biobank (INTERBIO-Bank) of maternal blood, maternal faeces and cord blood/placental samples from at least six populations with different risk profiles, including women at high risk for preterm delivery and IUGR/SGA because of malnutrition and/or infection. We shall follow a longitudinal and cross-sectional study design in two sub-studies. These samples will be used primarily to explore risk factors and biomarkers for the subgroups of IUGR/SGA and preterm delivery.
- PROGRAMME II: Conduct, in the first of a series of experiments, a hypothesis-testing, proof-of-concept study comparing DNA methylation patterns and micronutrient status in term AGA and IUGR/SGA newborns drawn from the INTERBIO-Bank.

Figure 1: INTERBIO-21st Study Flow Diagram

[figure not shown]

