##### **New INTERBIO-21st centres**

Women from the entire population attending for antenatal care from <14 weeks' gestation, irrespective of their risk profile for adverse pregnancy/neonatal outcomes, should be recruited for INTERBIO-Bank. However, to participate, women must be at least 18 years old and their pregnancy must have been conceived naturally. Women who have a BMI over 35 must also be excluded from the study as their weight will be a barrier to accurate ultrasound scans. All other women are eligible.

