Because of the different populations in the centres selected, all analyses in this case-control strategy will be stratified by centre, and will only be pooled if there is no statistical evidence of heterogeneity.

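### Appendix K, Programme II leaves the control source open and permits a least-risk source, which could select controls on nutrition, the hypothesised exposure

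*Protocol*

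**What the plan says.** Appendix K, Programme II, Study design, fixes the case source: "we will randomly select 500 term IUGR/SGA cases from the INTERBIO-Bank". Two control sources are then allowed. In the first, "controls will be taken either from the population at least risk within the" Fetal Study. The second reads "or from the total with normal outcomes from the entire study population, and matched with the cases". The choice is deferred: "A final decision will be made by the" Steering Committee. The section defines neither least risk nor the matching factors.

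The rest of Appendix K gives the context:

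- The Summary says that the biobank is built "from at least six populations with different risk profiles, including women at high risk for preterm delivery and IUGR/SGA because of malnutrition and/or infection".
- The inclusion criteria recruit women to the Fetal Study in both existing and new centres "irrespective of their risk profile for adverse pregnancy/neonatal outcomes".
- General Objectives states the exposure: "Our hypothesis is that maternal micronutrient deficiency" impairs fetal growth through altered DNA methylation.
- For the Neonatal Study, the text after Box 1 says that "all analyses in this case-control strategy will be stratified by centre". The operational definition of cases and controls matches on hospital and approximate date of birth. Neither rule is restated for Programme II.

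**The concern.** Controls in a case-control study should show how common the exposure is in the population that produced the cases. Here the cases come from every population in the bank, while one permitted control source is chosen for being at low risk. Appendix K ties high risk to malnutrition and infection, so choosing controls for low risk plausibly means choosing better-nourished mothers.

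If nutrition alters methylation at all, a case-control difference in methylation would then appear whether or not methylation has any bearing on growth. The micronutrient comparison planned in the same 500 cases and 500 controls would be tilted the same way. This is a defect in who is sampled, and an analysis plan written later could not supply controls who were never selected.

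**Working it through.** **1. What each reading of least risk implies.**

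- *Certain centres.* Some wording in Appendix K points this way. It contrasts three INTERGROWTH-21st centres with high-risk populations in resource-poor settings, and the sample-pooling paragraph takes its healthy reference samples from those three centres. The other centres would then supply cases but no controls, and case status would be confounded with centre. If centre were a matching factor, those cases could not be matched, so the option could not be carried out as written.
- *Certain women in every centre.* The inclusion criteria allow this reading. Centre can then be matched, but within each centre the controls are still chosen for low risk. Matching on centre leaves that selection in place.

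**2. Reproducing the plan's figure.** Table 1 of Appendix K (candidate-gene study, 1:1, α = 5.0×10⁻⁴, 80% power, methylated proportion 0.2 in controls and 0.3 in cases) gives 719 cases. With d = p₁ − p₀ and p̄ the mean of the two proportions:

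n′ = [z₁₋α/₂ √(2p̄(1−p̄)) + z₁₋β √(p₁(1−p₁) + p₀(1−p₀))]² / d²

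n = (n′/4) [1 + √(1 + 4/(n′d))]²

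With two-sided z = 3.481 and 0.842, n′ = 698.8 and n = 718.6, that is 719. The other 1:1 entries in this block (342, 204, 137, 99) reproduce to within one case.

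**3. Bias with no true effect.** The protocol gives no methylation figures by centre or risk group, so these inputs are assumptions:

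- methylated proportion 0.20 in low-risk populations (Table 1's control value) and h = 0.25 to 0.40 in high-risk populations;
- within any population, no difference between cases and controls;
- high-risk populations supply a share f = 40% to 60% of cases. This brackets 2 of 5 Fetal Study centres (2,500 pregnancies at 500 per centre, three of them INTERGROWTH-21st centres) = 40%, and 4 of the 7 listed sites = 57%;
- all 500 controls come from low-risk populations.

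The proportion in cases is p₁ = f·h + (1−f)·0.20, and the spurious odds ratio is [p₁/(1−p₁)] / [0.20/0.80]. The chance of significance is Φ((d − 3.481·SE₀)/SE₁), where SE₀ = √(2p̄(1−p̄)/500) and SE₁ = √([p₁(1−p₁) + 0.16]/500). The opposite tail is negligible.

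Middle example (h = 0.30, f = 50%): p₁ = 0.25 and OR = 0.3333/0.25 = 1.33. SE₀ = 0.02641 and SE₁ = 0.02636, so z = (0.05 − 0.0919)/0.02636 = −1.59 and the probability is 5.6%. Against the nominal 0.05%, that is about 110 times.

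| h | f = 40% | f = 50% | f = 60% |
|---|---|---|---|
| 0.25 | OR 1.13; 0.3% | OR 1.16; 0.6% | OR 1.19; 1.0% |
| 0.30 | OR 1.26; 2.5% | OR 1.33; 5.6% | OR 1.41; 10.9% |
| 0.35 | OR 1.41; 10.9% | OR 1.52; 24% | OR 1.63; 43% |
| 0.40 | OR 1.56; 30% | OR 1.71; 57% | OR 1.88; 80% |

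These probabilities carry no continuity correction. With it, 57% becomes 54%.

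**4. With matching source populations.** If controls have the same population mix as the cases, p₁ = p₀ in every cell, the odds ratio is 1.00 and the rate returns to 0.05%.

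**The case against.** The strongest reply is that nothing has been decided. The same sentence offers a second source, all normal outcomes in the whole study population, and says that controls are matched with the cases. The Steering Committee could choose that source and match on centre. This stands: the protocol permits a biased comparison and does not commit to one.

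A reader might infer that the high-risk centres would have no controls. The text does not say so. It speaks of a population at least risk, and the Fetal Study recruits women of all risk levels in every centre. Centre confounding therefore depends on an undefined term and on unnamed matching factors.

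A reader might also take a false-positive rate above 50% as the expected size. At methylation 0.30 in high-risk and 0.20 in low-risk populations, that needs every case to come from the high-risk side. The cases are a random draw from a bank that includes Oxford, Pelotas and Nairobi.

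Nor do the documents support calling any result uninterpretable. Micronutrients and methyl-donor markers are to be measured in all 1,000 newborn-mother pairs and correlated with methylation, and ethnic sub-groups are to be compared. This allows partial examination but does not undo selection on the exposure. Appendix K's Sample size section itself recognises possible selection bias from FGLS controls, but that caution is not carried into Programme II.

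**Conclusion.** The point holds as a fault in a permitted option. Cases and controls would not share a source population if the least-risk source were chosen, and the selection plausibly acts on the exposure under study. That part survives matching on centre. Confounding with centre is conditional on what least risk means and on whether centre is matched.

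The size is unknown. Under the stated assumptions the spurious odds ratio is 1.13 to 1.88, which reaches the smallest effect in Table 1 (1.71), and the per-locus false-positive rate is about 0.3% to 80% against 0.05%. The calculation treats the controls as wholly low-risk and the cases as a mixture. It illustrates scale and is not an estimate. The decision is still open, so the change is best made before samples are selected.

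**What to change.** In Programme II, Study design:

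1. Delete the least-risk control source.
2. Keep the second source, normal outcomes from the entire study population. Name centre and sub-study (Fetal or Neonatal) as matching factors, so that controls come from the same centres and sub-studies as the cases.
3. State that the centre-stratified analysis of the Neonatal Study applies here too.

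Sub-study matters because sampling differs. The protocol's section 1.11 (Oxford) takes maternal blood at booking in the Fetal Study and at delivery in the Neonatal Study, and Appendix K enrols Neonatal Study women on admission for delivery. The Nutritional status section of Programme II calls for booking blood.

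The cost is a few sentences. No extra recruitment should be needed, since 400 Neonatal Study controls per centre and 500 Fetal Study pregnancies per centre are already planned. There is a small scientific cost. The controls will be less uniformly healthy, and comparisons that use booking blood or serial fetal growth will be limited to cases and controls from the Fetal Study.

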### Methods

We have given considerable thought to the best technological platform for assessing methylation profiles and we have consulted widely with leading experts in the scientific community and industry. There are a large number of different platforms available and many more being developed; in general, there is an inverse relationship between the cost of analysis and the resolution/coverage of the genomic region being studied. At this stage, however, we have decided to use Methylated-Cytosine DNA Immunoprecipitation-Microarray Chip (MeDIP-Chip) followed by bisulfite-(BS) PCR and high throughput sequencing for validation of differentially methylated loci.

The approach is well described in a recently published proof-of-concept study assessing whether 'DNA methylation in a subset of genomic loci may connect end-stage cardiomyopathy with different etiologies'. In brief, these authors performed a preliminary analysis using MeDIP-Chip (Nimblegen, WI, US); validated differential methylation loci by BS-PCR and high throughput sequencing; identified three angiogenesis-related genetic loci that were differentially methylated with the BATMAN algorithm^26, and using quantitative RT-PCR, found that the expression of these genes differed significantly between cardiomyopathy hearts and normal controls.

However, we are aware that the samples may not be analysed for at least another two years by which time the technology is likely to have changed considerably, costs will have fallen and genome-wide profiling in large numbers of samples will be affordable. We are therefore in preliminary discussions with a number of companies, including Nanopore (Oxford, UK), <http://www.nanoporetech.com>, and Pacific Biosciences (Menlo Park, CA, US), <http://www.pacificbiosciences.com>, who may soon be able to offer high-throughput, single molecule sequencing. Whichever platform is used, however, the intention ideally is to analyse all samples in a centralised facility; in fact, this applies to all the experiments proposed in the proof-of-concept study.

